**Reports from the ISM**

The following reports may be submitted by the ISM: review report and immediate action report.

**Review Report**

The ISM will communicate in writing his/her findings and any concerns and recommendations to the Sponsor representative at PATH. If the ISM does not concur with the assessment provided by the local investigative staff, the written report will then be forward to the local PI in Pakistan, who must file a copy in the study files and submit the report as per local IRB policy.

**Immediate Action Report**

The ISM will notify the Sponsor representative of any findings of a serious and immediate nature including any recommendations to discontinue all or part of the trial, and the Sponsor representative will immediately inform the PI, other PATH investigators, and CDC. In additional to any verbal communications, recommendations to discontinue or substantially modify the design or conduct of a study must be conveyed in writing on the day of the ISM review.

- 1. **Study schema**

CHWs will recruit healthy infants between 4- 6 weeks of age on their routine surveillance

CHW will do the assessment of the infant through enrollment check list

Parents or caretaker of eligible infants will be provided transportation for required visits

Primary Health Care Center

Medical Officer

History and PE to assess eligibility

**Eligible Not eligible**

Consent requested by study

Physician

Exit

**Consent declined**

**Consent given**

Randomization into Arm 1, 2, 3

- 1. **Vaccination and Blood Draw Schedule.** Blood samples will be obtained at the scheduled visits just prior to the administration of vaccines.

**Arm 3**

Rotarix® Vaccination

n= 200

**Arm 2**

Rotarix® Vaccination

n= 200

**Arm 1**

Rotarix® Vaccination

n= 200

**Visit at 6 weeks**

- Pre vaccine blood draw
- EPI vaccination
- 1^st^ dose Rota virus vaccination

**Visit at 6 weeks**

- Pre vaccine blood draw
- EPI vaccination
- 1^st^ dose Rota virus vaccination

**Visit at 6 weeks**

- Pre vaccine blood draw
- EPI vaccination

**Visit at 10 weeks**

- EPI vaccination
- 1^st^ dose Rota virus vaccination

**Visit at 10 weeks**

- EPI vaccination
- 2^nd^ dose Rota virus vaccination

**Visit at 10 weeks**

- EPI vaccination
- 2^nd^ dose Rota virus vaccination

**Visit at 14 weeks**

- EPI vaccination
- 3^rd^ dose Rota virus

**Visit at 14 weeks**

- EPI vaccination
- 2^nd^ dose Rota virus vaccination
- sample on day’s 3 and 7 after vaccination

**Visit at 14 weeks**

- Blood draw
- EPI vaccination

**Visit at 18 weeks**

- Blood draw

**Visit at 18 weeks**

- Blood draw

**Visit at 18 weeks**

- Blood draw
  1. **Enrollment Time Period**

Enrolment will be completed over a period of one year so that all the seasons are covered. The rotavirus infections in Karachi are seasonal, with peaks in both summer and winter months which can influence baseline seroconversion. Refer to section 4.5

- 1. **Enrollment Schedule**

| ***Treatment Group*** | ***Number of Subjects*** | **Youngest (Y): 6wk, 0dy**  **Oldest(O): 7wk, 6dy** | **Y: 10wk, 0dy**  **O: 12wk, 6dy** | **Y: 14wk, 0dy**  **O: 17wk 6dy** |
| --- | --- | --- | --- | --- |
| Arm 1 | 200 | Standard EPI + Rotarix® | Standard EPI + Rotarix® | Standard EPI |
| Arm 2 | 200 | Standard EPI | Standard EPI + Rotarix® | Standard EPI + Rotarix® |
| Arm 3 | 200 | Standard EPI + Rotarix® | Standard EPI + Rotarix® | Standard EPI + Rotarix® |

*Standard EPI in Pakistan is OPV plus BCG at birth; DPT-Hep-B-Hib and OPV at 6, 10, and 14 weeks, and measles at 9 months and second year of life

- 1. **Sampling Collection and Handling**

3 ml of blood sample will be obtained by a trained health worker according to WHO standard procedures. Blood draws will be done at 6, 14 and 18 weeks of age. Blood samples from this study will be used only for rotavirus IgA and neutralizing antibody assay testing. Samples will be stored with a unique identification number specific for the study child.

- 1. **Lab Assay**

| ***6wks*** | ***10wks*** | ***14wks*** | ***18wks*** |
| --- | --- | --- | --- |
| **All arms:**  Rotavirus IgA (Serum)  Rotavirus Neutralizing Antibody (Serum) |  | **Arm 1 only**  Rotavirus IgA (Serum) | **All Arms**  Rotavirus IgA (Serum) |
|  |  |  |  |
|  |  |  |  |

- 1. **Laboratory Training for Rotavirus antibody assays**

We will make arrangements with the laboratory of [name] lab in Cincinnati, OH, USA to train one senior laboratory technician from our laboratory in performing rotavirus IgA. Since rotavirus neutralizing antibody assays are complicated and the number of samples that need to be tested for neutralizing assay is small, samples will be shipped to [name] lab in Cincinnati, OH for testing of neutralizing antibodies.

- 1. **Data Entry, Cleaning and Management**

All completed case report forms (CRFs) will be edited by the field RA at the PHCs and a second quality check on all forms will be done by the data RAs at the Data Management Unit (DMU). A data entry program (database and entry screens) will be created in MS Access 2007. Program will contain logical checking and will support double data entry. Dual entry error checking will be done on weekly basis and error report will be generated for corrections. After dual entry checking the data will undergo second phase of logical checking before analysis.

The database will reside on a central computer managed by the Data Manager. All data entry operators will access the program through the local network. The database will be regularly backed up every day on site and weekly off site on an external device and on the main university servers. All hard copies of the forms will be stored in two different locations: the first temporary location will be in the room where quality check, data entry and cleaning operations take place; permanent storage will be in a document storage room. Both storage rooms will be locked and moving of forms will be tracked using an Excel sheet.

- 1. **Data Analysis of Demographics**

The mean, range standard deviation of height in cm, weight in kg and of age in weeks will be calculated per group. The racial and gender composition per group will be presented.

- 1. **Analysis of immunogenicity**

Seropositivity will be defined as an anti-rotavirus IgA concentration ≥20 U/ml. Seroconversion will be defined as the detection of anti-rotavirus IgA concentration ≥ 20 U/ml in infants seronegative for anti-RV IgA at age 6 weeks before vaccination. The primary analyses will be performed on the according to protocol (ATP) cohort. Rotavirus IgA seroconversion rate (proportion of infants who have rotavirus IgA antibodies in serum sample) by age 18 weeks will be determined for infants in each arm who were rotavirus IgA –negative at 6 weeks of age. The primary endpoint will be the comparison of the rotavirus IgA seroconversion rate at age 18 weeks in arm 3, compared to the greatest IgA seroconversion rate for arm 1 (either the result from the 14 week samples or the 18 week samples). This latter aspect is included in order to provide the most relevant comparison between arms 1, 2 and 3 because both times since last dose of rotavirus vaccine and age at last blood draw can affect seroconversion estimates. Seroconversion rates will be compared between arm 1 and arm 3 using a Chi-square test. Confidence intervals (95%) for the differences in seroconversion rates will also be calculated. Rotavirus IgA GMC (geometric mean concentration) will be calculated and compared between the arms using a t-test. As described above for seroconversion, this would be at age 18 weeks for arms 1 and 3, and the highest result from the 14- and 18 week sample for arm 2.

- 1. **Role of Maternally derived Rotavirus Neutralizing antibodies in the immunogenicity of Rotavirus vaccine:**

The distribution of the level of maternally-derived rotavirus antibodies in the 6 week serum samples (among those infants who were rotavirus IgA negative at age 6 weeks and completed the study ATP) will be examined. The independent effect of the level of maternally-derived neutralizing antibody level on the rate of rotavirus IgA seroconversion by age 18 weeks will be assessed using logistic regression. Vaccine schedules will be included {(Arm 1 vs. Arms 3(primary) and Arm 1 vs. Arm2 (secondary)} as an independent variable and effect modification by neutralizing antibody level will be examined. Exploratory analyses will be performed for correlation between maternally-derived neutralizing antibody level and rotavirus IgA level at age 18 weeks among the two vaccine schedule categories

**Study B: Impact of withholding breastfeeding around the time of Rotarix® vaccination on the immunogenicity of Rotarix® vaccine.**

- 1. **
[figure not shown]
Study Site**

The study will be conducted at one site in an urban- squatter settlement area, Ibrahim Haidry in Karachi where the Aga Khan University’s Department of Paediatrics and Child Health has demographic surveillance in place, including pregnancy and newborn surveillance. The annual birth cohort in the area is approximately 1800 infants. The site is about 30 minutes driving distance from the Aga Khan University Medical College and Hospital campus. A GIS map of the site is available. The Department will provide EPI immunizations at this location.

- 1. **Study Design**

This study will compare the immunogenicity of Rotarix ® vaccine in relation to the timing of breast feeding. The two arms of the study will receive the EPI vaccines according to the usual schedule in Pakistan at ages 6, 10 and 14 weeks and Rotarix® vaccine at 6, 10, and 14 weeks of age. In arm 1, mothers would be asked to breast feed immediately before administration of the Rotarix dose. In arm 2, mothers would be asked to withhold breast feeding for one hour before and one hour after each Rotarix®dose.

Infants potentially eligible for the study will be identified by the CHWs during their routine household surveillance, and will be brought to the PHC at 4 weeks of age or at the time of first contact with the baby. In the PHC, infants will undergo history and physical examination by the study medical officer to determine eligibility. Study procedures will be explained to the mothers, including the need to withhold breastfeeding or to breastfeed at time of the vaccine doses, depending on the study arm. Consent will be asked from the parents of infants who are eligible. After obtaining consent, infants will be randomized into the breast feeding with holding or immediate breastfeeding arms.

Mothers who earlier provided consent and were randomized to the immediate breastfeeding group will be picked up at their home approximately 1 hour before the expected immunization time and instructed not to breastfeed until the indicated time. They will be taken to the clinic, infant blood sample will be obtained, routine EPI immunization will be given and mother will be asked to breastfeed the baby for at least 20 minutes. CHW staff will observe the breastfeeding. The Rotarix vaccine will be given, and then baby will be observed for 20 minutes to document if any vomiting occurred.

Mothers who earlier provided consent and were randomized to the withholding breastfeeding group will be picked up at their home approximately 1 hour before the expected immunization time and instructed not to breastfeed until the indicated time. They will be taken to the clinic, infant blood sample will be obtained, routine EPI immunization will be given, Rotarix vaccine will be given, and then mother will be asked to not breastfeed for one hour after the dose. CHW staff will observe the mother and infant during this period and document withholding of breastfeeding and to document if any vomiting occurred. After the 1 hour period, the mother will be able to breastfeed the infant if desired.

On the day of each vaccine visit, the mother will be asked to express 10 ml of breast milk into a study container while the CHW is present in the home to assist as needed or in the clinic and to refrigerate the sample as soon as it is expressed.

At age 6, 14 and 18 weeks, in breast feeding withholding arm 1 ml of oral fluid (OF) will be taken from infants in order to determine the correlation of IgA in OF and serum. Arm 1 provides an ideal setting to assess the value of non-invasive OF assays for rotavirus immune response, avoiding the potential contamination from breast milk.

- 1. **Sample Size consideration:**

Target enrollment would be 400 infants (200 each in each group) to be able to detect a difference in seroconversion rate of at least 17.5% between the withholding breastfeeding group and the immediate breastfeeding group, if such a difference truly exists.

Assumptions used for calculation of sample size are an estimated seroconversion rate in the immediate breastfeeding infants of 45% at age 18 weeks and in the withholding breastfeeding infants of 62.5% at age 18 weeks; power at 0.85, and a two-sided alpha of0.05. Using a Chi-square test and assuming 20% drop out and 5% baseline IgA seropositivity at 6 week, the estimated sample size needed in each group is 191.

- 1. **Study schema**

CHWs will identify healthy infants younger than 5 weeks of age on their routine surveillance using the enrollment checklist

Parents or caretaker of eligible infants will be provided transportation for required visits to PHC

Child referred to PHC for enrollment and randomization at 5 weeks

History and physical examination by PHC Medical Officer to assess eligibility

Consent asked from parents of eligible infants

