**3.4 Inclusion Criteria**

- - 6 weeks 0 days to7 weeks 6 days age at the time of enrollment.
  - Healthy infant free of chronic or serious medical condition as determined by history and physical exam at time of enrollment into in the study.
  - Written informed consent obtained from the parents or guardians.
  1. **Exclusion Criteria**
- Hypersensitivity to any of the vaccine components.
- Use of any investigational drug or vaccine other than the study vaccine within 30 days of first dose of study vaccine or during the study.
- Use of any immunosuppressive drugs.
- Previous intussusceptions or abdominal surgery.
- Enrolment in any other trial (Simplified Antibiotic Therapy for Neonatal Sepsis Trial, Management of Omphalitis Trial).
- Birth weight less than 1500 grams; or if birth weight is unknown, weight less than 2000 grams on or before 28 days.
- Immunoglobulin and/or blood products use since birth or during the study period.

Rotavirus vaccine administration should be postponed in subjects who, per the clinician’s assessment:

- - Have vomited during each of the last three feedings
  - Are recommended for hospitalization at the visit
  - Are suffering from acute febrile illness. Acute febrile illness is defined as temperature ≥ 38.0^o^ measured by rectal or axillary thermometer (Meet WHO criteria for moderate to severe dehydration (= those needing ORS rehydration in the facility or intravenous rehydration).
  - EPI vaccinations will be provided or postponed as per the clinician’s assessment and according to standard practice.
  1. **Elimination Criteria During the Study**
- Rotavirus IgA seropositivity in the blood specimen obtained at age 6 weeks, if the results become available before the time additional rotavirus vaccine doses are due to be given or additional blood draws or other samples are due to be obtained. These children will not be included in the final analysis, since they are already seropositive and cannot seroconvert due to rotavirus vaccine. If the 6-week IgA results become available before the time additional rotavirus vaccine doses are due or study samples are scheduled to be obtained, these children will not receive further rotavirus vaccine doses or undergo further blood draws or study sample collection; however, we will ensure that they continue to receive the routine EPI vaccines.
- Infants who develop intussusceptions during the study will not receive additional doses of rotavirus vaccine.

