- Infants who have a hypersensitivity reaction due to rotavirus vaccine and who have not yet received their final dose of rotavirus vaccine.
  1. **Contraindication of the Rotavirus Vaccine**
     - - Hypersensitivity reaction due to the rotavirus vaccine
       - Infants who develop intussusceptions during the study
  2. **Recruitment Process**
  - Eligible infants will be recruited through the community health workers on their routine surveillance in the Ali Akber Shah Goth.
  - The CHWs will approach the families who have an infant between 4 to 6 weeks of age. Parents or caretaker will be briefed about the study and visits to be made at PHC for vaccination and blood draws.
  - If the parent/caretaker is interested in the study, CHW will evaluate the infant by enrollment check list.
  - Parents or caretaker of eligible infants will be provided transportation for visits to be made at PHC for enrollment, vaccination and blood draws.
  - At 6 weeks of age, infant of interested parents will be brought to the PHC where infants will undergo history and physical examination. Consent will be obtained and Infants will be enrolled if they meet the eligibility criteria.
  - Eligible Infants will be randomly allocated to one of the three groups using randomly generated computer assignments, allocated in sealed envelopes to be opened at the time of enrolment.
  - Baseline information on socio – demographics background, pregnancy, prenatal and delivery details, medical and vaccination history will be recorded.

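### Study A: the child-level sample number, with a 14-week serum in arm 1 only, can let the laboratory recognise arm 1; the protocol describes no masked assay

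*Protocol*

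**What the plan says.** - **Labelling.** Protocol section 3.13 (Sampling Collection and Handling): "Samples will be stored with a unique identification number specific for the study child". This is one number per child. Recoding before assay is not mentioned.
- **Assay schedule.** The table in section 3.14 lists serum IgA at 6 and 18 weeks for all arms and at 14 weeks for arm 1 alone. In the visit schema (section 3.10), the only 14-week box with a blood draw is the one without a rotavirus dose, which is arm 1.
- **Text that does not fit.** Section 3.13 also says, with no arm restriction, "Blood draws will be done at 6, 14 and 18 weeks of age". In section 3.18 the sentence on geometric mean concentration uses "the highest result from the 14- and 18 week sample for arm 2".
- **Laboratory.** Section 3.15 plans "to train one senior laboratory technician from our laboratory in performing rotavirus IgA". Study B refers to the same section for its serum IgA.
- **Endpoint.** Section 3.18: "Seropositivity will be defined as an anti-rotavirus IgA concentration ≥20 U/ml". Among infants IgA-negative at 6 weeks, arm 3 at 18 weeks is "compared to the greatest IgA seroconversion rate for arm 1 (either the result from the 14 week samples or the 18 week samples").
- **Allocation.** Section 3.8: assignments are "allocated in sealed envelopes to be opened at the time of enrolment". No placebo is described.
- **Use of results by child.** Section 3.6 acts on IgA results during follow-up: "If the 6-week IgA results become available before the time additional rotavirus vaccine doses are due or study samples are scheduled to be obtained", a seropositive child gets no further rotavirus doses or study samples.

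**The concern.** The schedules differ visibly between arms and no placebo is described, so families and clinic staff will know the allocation. The assay is the one step of endpoint assessment that could easily be masked.

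The stated labelling and the arm-specific sampling together work against that. Under the assay table, a Study A serum taken at 14 weeks can only come from arm 1, and that tube may itself supply arm 1's value for the primary comparison. Because all of a child's tubes share one number, the same inference reaches the 18-week tube.

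The endpoint is a yes/no call at 20 U/ml. If the reader knows the arm, decisions to repeat or accept a result near the cutoff could differ between arm 1 and arm 3, the two sides of the primary contrast.

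**Working it through.** **1. The plan's own figure (background only).** Section 3.3 assumes 35% versus 52.5%, power 0.85 and two-sided alpha 0.05, with 20% dropout and 5% seropositive at 6 weeks.

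n = [1.960·√(2·0.4375·0.5625) + 1.036·√(0.35·0.65 + 0.525·0.475)]² / 0.175² = 143 per arm.

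143/0.75 = 190.7, so 191, the stated figure. (143/(0.80·0.95) gives 189.) Nothing below disputes this. At the enrolment target, 200·0.80·0.95 = 152 evaluable per arm.

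**2. What a 14-week tube reveals in Study A, under each reading of the text.**
- *Drawn and assayed in arm 1 only (table and schema):* every 14-week serum is arm 1.
- *Drawn in all arms, assayed in arm 1 only (section 3.13 with the table):* a 14-week tube sent for assay still marks arm 1.
- *Assayed in arms 1 and 2 (suggested by the geometric mean sentence):* the tube no longer singles out arm 1, but it excludes arm 3, so the primary contrast is still exposed.
- *Assayed in all arms:* the signal disappears. No passage clearly states this.

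**3. How many infants.** Take the first reading and assume 80% to 100% of arm 1 attend the 14-week draw.
- Arm 1 infants identifiable: 200·0.80 = 160 to 200·1.00 = 200.
- A child without a 14-week tube is outside arm 1 with probability 400/(400 + 40) = 91% up to 400/400 = 100%.

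**4. If Study A and Study B tubes cannot be told apart.** Both Study B arms (400 infants) have 14-week serum IgA. With equal attendance, a 14-week tube comes from Study A arm 1 with probability 200/(200 + 400), or 1 in 3.

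**5. What an assessment bias would do (illustration only).** The shifts and rates are assumed. This is a simple two-arm comparison that ignores the rule taking the greater of two arm 1 rates.

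With 45% in both arms, SE = √(2·0.45·0.55/152) = 0.0571. For a net shift d in one arm, the rejection probability is Φ(d/SE − 1.96) + Φ(−d/SE − 1.96).

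| Net shift | Infants of 152 | d/SE | Two-sided error |
|---|---|---|---|
| 0 | 0 | 0 | 5.0% |
| 2 points | about 3 | 0.35 | 6.4% |
| 3 points | about 5 | 0.53 | 8.2% |
| 5 points | about 8 | 0.88 | 14.2% |

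A second error model has a fraction of arm 1 positives missed, with no true difference. It is evaluated at the protocol's two planning rates:

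| Positives missed in arm 1 | True rate 35% | True rate 52.5% |
|---|---|---|
| 2% | 5.2% | 5.4% |
| 5% | 6.2% | 7.4% |
| 10% | 9.9% | 15.0% |

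**The case against.** The strongest reply is that the protocol is silent on masking and does not reject it. The labelling sentence concerns storage. It does not say what label the analyst sees or in what order tubes are run. Results must be linked to the child, so a child number is ordinary, and the time line lists standard operating procedures, which could hold a coding step. This stands. A reader might infer that masking of arm 1 is impossible, but recoding aliquots before assay is compatible with everything written.

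The route also needs two facts that the protocol does not give: the visit must be visible on the tube, and Study A must be distinguishable from Study B. Without the second, a 14-week tube is weak evidence of arm. This stands too, and makes the point conditional.

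A reader might take it as settled that only arm 1 has a 14-week serum. The table and schema agree on this, but the unrestricted draw sentence and the arm 2 sentence do not.

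A reader might also take the error rates as a forecast. They are not: the protocol gives no density of results near 20 U/ml and no repeat-test practice, and 45% is not a Study A planning rate. IgA is a quantitative assay, which limits the room for judgement, and the technician to be trained is a senior one.

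Finally, the mechanism does not extend to the other components. Study B has the same serum schedule in both arms, and Study C has no randomised arms.

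What remains is that the stated labelling and the arm-specific assay schedule create an avoidable route to unmasking, and nothing in the protocol closes it.

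**Conclusion.** The point holds for Study A in conditional form: the laboratory can identify arm 1. The documents do not show that it will, or that results would be biased.

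It rests on three assumptions: tubes are assayed under the child number, the visit is visible, and Study A tubes can be told from Study B tubes. If these hold, 160 to 200 of the 200 arm 1 infants are recognisable at 14 weeks and, through the number, at 18 weeks. Arms 2 and 3 cannot be separated from each other this way under the assay table, but the primary contrast is arm 1 against arm 3. That the trial is open-label is inferred from the absence of placebo and masking; the protocol does not use the term.

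The size of any bias is unknown. The assumed shifts show only that a handful of reclassified infants in one arm would matter: a net 3 points is 3/17.5 = 17% of the planned difference. This is a minor but inexpensive improvement, and no figure in the protocol is shown to be wrong. The conflicting statements about 14-week samples need reconciling in any case.

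**What to change.** For Study A, amend section 3.13 as follows:
- Assay sera under random specimen codes that show neither child, visit nor arm.
- Let the data manager hold the key and return the 6-week results that the elimination rule needs.
- State that the laboratory is masked to allocation.
- Set the rule for repeat tests near 20 U/ml before testing starts.
- Release the key only after the IgA file is locked.

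Separately, reconcile the draw sentence in section 3.13, the assay table in section 3.14, the schema and the geometric mean sentence in section 3.18, so that it is clear which arms have a 14-week serum.

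The cost is a code list with printed labels and slightly slower return of 6-week results. That delay matters somewhat, because the elimination rule applies only when those results arrive before the next dose or sample. No extra infants, visits, blood or assays are needed, and the sample size is unchanged.

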Target enrollment would be 600 infants; 200 in each of the arms 1,2 and 3. Assumptions used for calculation of sample size are estimated seroconversion rate in arm 1 of35% (11), and in arm 2 and 3 of 52.5%(investigational), power at 0.85, and alpha error of 0.05, using a two-tailed t-test & Chi-square test and assuming 20% drop out and 5 % expected IgA seropositive at 6 weeks. The estimated sample size needed in each group is 191.

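### Study A's primary comparison sets arm 3's single 18-week rate against the larger of two observed arm 1 rates, which tilts the third-dose estimate toward arm 1 when those two rates are close

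*Protocol*

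**What the plan says.** The analysis of immunogenicity for Study A (Protocol, section 3.18) defines the primary endpoint as arm 3's rotavirus IgA seroconversion rate at 18 weeks "compared to the greatest IgA seroconversion rate for arm 1 (either the result from the 14 week samples or the 18 week samples". The reason given is that this is the most relevant comparison "because both times since last dose of rotavirus vaccine and age at last blood draw can affect seroconversion estimates". The test is fixed in the same paragraph: "Seroconversion rates will be compared between arm 1 and arm 3 using a Chi-square test". So is the interval: "Confidence intervals (95%) for the differences in seroconversion rates will also be calculated". Nothing is said about allowing for the choice between the two arm 1 rates.

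The laboratory assay table for Study A (section 3.14) lists the 14-week test as "Arm 1 only Rotavirus IgA (Serum", while all arms are tested at 18 weeks.

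The sample size (section 3.3) uses one arm 1 figure, "estimated seroconversion rate in arm 1 of35% (11", against 52.5% in arm 3, with "power at 0.85, and alpha error of 0.05". It does not say whether 35% is the 14-week rate, the 18-week rate or the larger of the two.

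**The concern.** The larger of two observed proportions is on average higher than either true proportion when those are similar. Arm 3 gets no such second look, so the difference between arms is shifted toward arm 1. The chi-square test and the interval treat the selected rate as if it had been named in advance. The shift falls on the trial's headline question, whether a third dose adds to the 6- and 10-week schedule.

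The rule also leaves the question itself to the data. Arm 1's last dose is at 10 weeks and arm 3's is at 14. Using arm 1 at 14 weeks puts both arms about four weeks after their last dose but at different ages. Using arm 1 at 18 weeks puts both arms at the same age, but about eight and four weeks after their last dose. These are different comparisons, and taking the larger rate commits to neither.

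**Working it through.** **1. The plan's own figure.** Inputs from section 3.3: p1 = 0.35, p3 = 0.525, two-sided alpha 0.05, power 0.85, 20% dropout, 5% seropositive at baseline. With pooled rate p = 0.4375:

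n = [1.96·√(2·p·(1−p)) + 1.036·√(p1(1−p1) + p3(1−p3))]² / (p3−p1)² = (1.375 + 0.716)² / 0.175² = 142.7, so 143 evaluable per arm.

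143 / 0.75 = 190.7, so the stated 191 is reproduced. Enrolling 200 gives 200 × 0.80 × 0.95 = 152 evaluable. For a single pre-fixed arm 1 rate, power is 85% at 143 and 87% at 152.

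**2. Size of the selection bias.** Assume both true arm 1 rates are 35%, and let d be the proportion of infants whose status differs between the two draws. The protocol gives no value for d, so 10 to 30% is an assumption. The difference between the two observed arm 1 rates has standard deviation √(d/n), and the larger one exceeds 35% on average by

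bias = ½·√(2/π)·√(d/n).

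For d = 0.20 and n = 143: 0.399 × √(0.20/143) = 0.399 × 0.0374 = 1.5 points.

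**3. Effect on test and power.** Simulation, 400,000 trials per setting: paired 14- and 18-week results in arm 1, one binomial result in arm 3, uncorrected chi-square test on the larger arm 1 rate. The null columns set arm 3 at 35% as well, with n = 143.

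| Discordance d | Bias, n = 143 | Bias, n = 152 | Null: favours arm 3 | Null: favours arm 1 | Power, n = 143 | Power, n = 152 |
|---|---|---|---|---|---|---|
| 10% | 1.1 points | 1.0 points | 1.5% | 3.5% | 81% | 83% |
| 20% | 1.5 points | 1.4 points | 1.0% | 4.0% | 79% | 82% |
| 30% | 1.8 points | 1.8 points | 0.7% | 4.2% | 77% | 81% |

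The two null tails, nominally 2.5% each, become unequal but still sum to about 5%. Coverage of the 95% interval stays at about 95%.

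**4. When the loss disappears.** Keep 35% as the larger true rate and lower the other, over the same range of discordance:

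- 2 points lower: power about 82 to 84% at n = 143 and 85 to 86% at n = 152.
- 5 points lower: about 84 to 85% and 87%, so almost nothing is lost.
- If no seroconverted infant reverts, the 18-week rate can never be below the 14-week rate. The rule then always picks 18 weeks and there is no selection bias.

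**5. Why the time point of the 35% matters.** If 35% is the 18-week rate and the true 14-week rate is 40%, power at n = 152 is 57 to 58%. That comes mainly from the true contrast shrinking to 52.5 − 40 = 12.5 points, not from the selection.

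**6. Natural exposure if 14 weeks is selected.** Study C's sample size section quotes background seroconversion from under 5% to 20%. Assume 5 to 20% accrues at a constant rate over the 12 weeks from age 6 to 18 weeks. The four weeks from 14 to 18 then add 1 − 0.80^(4/12) = 7.2% at the upper value and 1 − 0.95^(4/12) = 1.7% at the lower. Applied to the 65% still seronegative, that is 4.7 and 1.1 points that arm 3 could gain over arm 1 without any vaccine effect. This runs opposite to the selection bias.

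**The case against.** The rule is pre-specified, mechanical and reasoned. Time since last dose and age at the draw both matter, and giving arm 1 its better result is a cautious way to handle that: it makes a false claim for the three-dose schedule less likely, not more. Equal true rates are the least favourable case for the selection. At 20% discordance they imply that 10 of every 35 infants positive at 14 weeks have reverted four weeks later, exactly balanced by new conversions, and nothing in the protocol supports that figure. Enrolling 200 rather than 191 absorbs part of any loss. Fixing 18 weeks has a cost too, because arm 1 is then measured further from its last dose, which favours arm 3 if IgA wanes.

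Most of this stands as a limit on size. It does not remove the asymmetry. A stated reason explains the rule but does not correct the estimate, and the larger rate controls neither of the two factors the reason names. Where the rule does no harm, it also does nothing that a fixed time point would not do.

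Three stronger readings are tempting, and the document does not support them:

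- **The type I error or the coverage fails.** Both totals stay near nominal. The fault is the unequal tails and the shifted estimate.
- **The stated power is simply not delivered.** That depends on the gap between the two arm 1 rates, on how often infants change status, and on what the 35% refers to. The protocol gives none of these.
- **An infant positive at either draw counts as seroconverted.** The wording compares two arm-level rates, one from each set of samples, so no figure should be built on a per-infant reading.

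**Conclusion.** The point holds as a bias in the primary estimate and an undecided comparison. If both true arm 1 rates are 35% and 10 to 30% of infants are discordant between draws (assumed), the third-dose effect is understated by about 1 to 2 points. Null rejections split roughly 1% for arm 3 and 4% for arm 1. Power is about 77 to 81% at 143 evaluable per arm and 81 to 83% at 152, against the stated 85%. These are conditional sizes: with a gap of about 5 points below 35% the loss is negligible, and with permanent seroconversion the selection bias is zero.

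Two faults do not depend on these assumptions. The data decide whether the arms are matched on age or on time since last dose, and the sample size does not say which arm 1 rate it uses. The same paragraph also contradicts itself: the sentence on geometric mean concentration refers back to the seroconversion rule, yet it uses 18 weeks for arm 1 and gives the highest-of-two treatment to arm 2. The assay table has no 14-week IgA result for arm 2.

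**What to change.** In section 3.18, delete the greatest-rate rule and name one arm 1 time point for the primary comparison. Eighteen weeks is a reasonable choice because it matches arm 3 on age and natural exposure. Report arm 1 at 14 weeks against arm 3 at 18 weeks, which matches time since last dose, as a named sensitivity analysis. Fixing 14 weeks as primary with the roles reversed would also remove the selection. If the sponsor prefers to keep the larger rate, the test, interval and power should be calibrated by resampling arm 1's paired results.

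In section 3.3, state which time point the 35% refers to. Reconcile the geometric mean sentence with the assay table, so that arms and time points agree.

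The cost is about one paragraph of wording, with no new samples or visits. The downside of choosing 18 weeks is unequal time since last dose in the primary contrast, which the sensitivity analysis addresses. The change should be made before the data are analysed.
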